### 2.4. Randomization and Treatment Allocation

Subjects will be selected during their psychiatry consultations following the stabilization of their pathology. If they meet the inclusion/exclusion criteria, they will be informed about the possibility of participating in the study, including its content and purpose. After being provided with an informed consent form and signing it, they will be randomly assigned to either the experimental or control group. Randomization will be conducted using a computer-generated random list. As participants are offered the opportunity to join the study, they will be assigned a number from the list in sequential order. The psychiatrist who refers the participants will not have access to the randomization list, ensuring allocation concealment. On the other hand, the psychiatrist responsible for administering the psychometric scales will be blinded to the intervention.

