### 2.3. Participants

The inclusion criteria for the present study will include the following: (a) patients admitted to the EIP due to a (b) FEP within the last 5 years, (c) with a diagnosis of psychosis from the F2 spectrum or an affective disorder with psychotic symptoms as per the ICD-10 [36].

Exclusion criteria will include (a) cognitive inability to learn or a comorbid diagnosis of an intellectual disability that interferes with the study procedures, (b) a comorbid diagnosis of neurological pathology, (c) the presence of language or comprehension alterations that prevent accurate data collection, (d) being prescribed a hypoglycemic drug before or during the study, or (e) refusal to participate. No patients will be excluded based on their special dietary needs (e.g., celiac disease, veganism, special diets) or a diagnosis of MetS before the start of the intervention. The primary consideration will be the individual’s desire to improve their weight or metabolic status. A participant will be considered a drop-out if they miss 2 or more of the first 6 consultations, are admitted to the hospital due to psychotic relapse, and/or experience psychopathological decompensation characterized by a score of 5 or higher on items P1 (delusions), P2 (conceptual disorganization), P3 (hallucinatory behavior), P6 (suspiciousness, persecution), P7 (hostility), and/or G8 (uncooperativeness) on the Positive and Negative Symptoms Evaluation Scale (PANSS) [37], and/or exhibit clinically significant self-directed or outwardly aggressive behavior.

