## Figures and Tables

**Table 1 nursrep-15-00003-t001:** Schedule of enrolment, interventions and assessments.

	Enrolment	Allocation	Post-Allocation							
TIMEPOINT	0	0	w 1	w 3	w 5	w 8	w 12	w 16	w 24	w 48
ENROLMENT:										
Eligibility screen	X									
Informed consent	X									
Allocation		X								
INTERVENTIONS:										
Mental health nurse consultation			X	X	X	X	X	X		
Aims and giving patients handbook			X							
Calorie counting errors and food to avoid				X						
Insulin and fats, proteins and CH					X					
Tips and feeding protocols						X				
Physical activity type							X			
Follow-up and counselling								X		
Treatment as usual										
ASSESSMENTS:										
Weight	X	X	X	X	X	X	X	X	X	X
Anthropometric variables (height, blood pressure, lab test…)			X						X	X
Scales (PANSS, HAM-D, EQ-5, IPAQ)			X						X	X

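### The drop-out rule uses an absolute PANSS item score with no baseline reference, entry has no matching condition, and the first PANSS is scheduled after allocation

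*Protocol article*

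**What the plan says.** Four parts of the Protocol article bear on this.

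- **Entry criteria (section 2.3).** The inclusion criteria are admission to the programme, time since the first episode, and diagnosis: "c) with a diagnosis of psychosis from the F2 spectrum or an affective disorder with psychotic symptoms as per the ICD-10 [36". The exclusions cover cognition, neurology, language, medication and refusal, and the list ends with "d) being prescribed a hypoglycemic drug before or during the study, or (e) refusal to participate". No criterion in either list concerns symptom severity.
- **Selection (section 2.4).** The one condition on psychiatric state is here: "Subjects will be selected during their psychiatry consultations following the stabilization of their pathology". No scale or score is attached. The next step is "After being provided with an informed consent form and signing it, they will be randomly assigned to either the experimental or control group".
- **Drop-out rule (section 2.3).** Among other grounds, participants are drop-outs if they "experience psychopathological decompensation characterized by a score of 5 or higher on items P1 (delusions", and likewise for P2, P3, P6, P7 and G8. The rule refers to no baseline score and no assessment time.
- **Schedule (Table 1).** The row "Scales (PANSS, HAM-D, EQ-5, IPAQ) X X X" has its three marks at weeks 1, 24 and 48, all under the post-allocation heading. The enrolment and allocation columns are empty in that row, although weight is marked in both. Section 2.5 places the test battery at the start of the study without saying whether that is before or after allocation.

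**The concern.** The exit rule is numerical and the entry rule is not, and no rating links them before randomisation. Clinical stability and an item score below 5 are different things: a patient can be stable with a residual symptom that rates 5. Section 2.4 also describes the referring psychiatrist separately from the psychiatrist who administers the scales, so the two judgements may come from different people.

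Two things are at stake. First, someone could be classed as a drop-out at the first rating for a state that existed before randomisation and that a rating already in the plan would have shown. Second, the baseline for psychopathology, quality of life and physical activity, all of them secondary aims, is scheduled after allocation in an open-label trial. At week 1 participants can know their arm, and those in the intervention arm are having their first consultation.

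**Working it through.** **1. Follow one participant through the text.** Take a patient with a stable P1 score of 5.

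| Step | Source | Result |
|---|---|---|
| Inclusion and exclusion criteria | Section 2.3 | No symptom item, so eligible |
| Judged clinically stable | Section 2.4 | Selected |
| Consent, then random assignment | Section 2.4 | Randomised, no PANSS taken |
| First PANSS, week 1 | Table 1 | P1 = 5 is recorded |
| Item score of 5 or higher | Section 2.3 | Score part of the drop-out rule is met |

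The patient's condition has not changed between the first row and the last. Week 1 is one of only three scheduled occasions on which the PANSS part of the rule can be applied, and nothing in the rule excludes it.

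**2. Reproduce the plan's sample size.** Inputs from section 2.9: difference 5%, SD 7.5%, power 80%, two-sided alpha 5%.

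- Normal approximation: n per arm = 2 × (1.960 + 0.842)² × (7.5/5)² = 2 × 7.85 × 2.25 = 35.3, rounded up to 36, or 72 in total.
- Two-sample t-test: 36.3 per arm, rounded up to 37, or 74 in total. This matches the plan.

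**3. Room for loss.**

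- 88 − 74 = 14 participants can be lost before the number falls below the requirement.
- The planned 20% loss is 0.20 × 88 = 17.6, which leaves 88 × 0.80 = 70.4 completers, already below 74.

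So the sample has no spare capacity for avoidable losses.

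**4. Sensitivity, for illustration only.** Let f be the share of the 88 who already score 5 or more at week 1. The documents give no value for f. If these participants are lost and the planned 20% then applies to the rest, completers = 88 × (1 − f) × 0.80. Power is for the two-sample t-test on the plan's own difference and SD.

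| f | People (88 × f) | Completers | Power |
|---|---|---|---|
| 0% | 0 | 70.4 | 78.7% |
| 2% | 1.8 | 69.0 | 77.9% |
| 5% | 4.4 | 66.9 | 76.6% |
| 10% | 8.8 | 63.4 | 74.3% |

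If the 20% allowance is meant to cover these cases as well, the first row applies throughout and nothing further is lost.

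**The case against.** The strongest reply is that the drop-out rule speaks of experiencing decompensation, which in ordinary use is a new worsening after entry, with the PANSS items only describing it. On that reading a stable patient with an unchanged score of 5 has not decompensated, and there is no conflict. This reading is reasonable and may be what the authors intend. However, the definition they give is an absolute level, and it does not tell staff how to treat a 5 at week 1. What stands is an ambiguity with a practical consequence, and not a flat contradiction.

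A reader might infer more than the text supports:

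- **That the missing definition of stabilisation is itself a fault.** An article may leave that detail to the full protocol. The point rests on how the stated exit rule and the stated schedule fit the stated entry rule.
- **That severity at entry cannot be told apart from later worsening.** It can. A qualifying score at week 1 is severity at or near entry, and a first qualifying score at week 24 or 48 is later change.
- **That a sizeable share of participants is affected.** Nothing in the documents supports any particular share, and selecting stable patients should keep it low.
- **That the comparison is biased.** Severity present before randomisation is unrelated to arm except by chance, and the psychiatrist giving the scales is blinded. The plausible cost is precision.
- **That these participants' data are certainly lost.** The article says they are counted as drop-outs. It does not say that follow-up ends or that their data are excluded.

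**Conclusion.** The point holds as a mismatch between the entry condition, the drop-out rule and the schedule. As written, a person can be randomised while already at the score that defines drop-out, and the plan does not say whether that counts.

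Its size is uncertain and probably small. The number affected may be near zero. In the illustration, an extra 5% lost moves power from 78.7% to 76.6%, provided that those participants really are lost and that the 20% allowance does not already include them. The reason to act is that the loss is avoidable, the margin is only 14 participants, and the correction is cheap. The same correction gives the secondary outcomes measured by the scales a true pre-allocation baseline. This should be changed, but it does not threaten the primary comparison.

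**What to change.** 1. In Table 1, move the first PANSS, and the other baseline scales with it, from week 1 to the enrolment column, before allocation. Make the start-of-study timing in section 2.5 agree.
2. Reconcile sections 2.3 and 2.4 with Table 1, so that the plan states whether an item score already present at the baseline rating counts as decompensation under the drop-out rule. Which clinical threshold or rule applies is for the sponsor to decide.

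Cost: no assessment is added, because the rating is already planned and weight is already measured at enrolment and allocation. The rating has to be arranged slightly earlier, which may delay randomisation briefly for some participants.

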### 2.5. Intervention

The study intervention will consist of a series of 8 nursing consultations with a specialized mental health nurse, who is trained in teaching healthy habits to individuals with psychosis and understands the unique factors influencing this group. The nurse will also be skilled in using the therapeutic relationship as a tool for habit modification.

During the first two months, 4 consultations will be held, focusing on educating patients about dietary habits based on the carbohydrate–insulin theory of obesity and physical activity, following a manualized intervention previously designed by a team composed of a mental health nurse, a nutrition and dietetics graduate, and a psychiatrist. This guide has been designed based on the consensus report of the American Diabetes Association for nutrition therapy for diabetes and prediabetes [26], as well as incorporating insights from clinical experience with individuals with a first episode of psychosis. The next two visits will take place 3 and 4 months after the first visit, respectively. Visit 7 will be held after 6 months to evaluate the intervention’s effectiveness, and visit 8 at 12 months. During all visits, weight will be monitored as a reinforcement element.

At the beginning of the study, and at 6 and 12 months from the start of the intervention, a battery of tests will be conducted, including analytical samples, vital signs, anthropometric measurements, and scales to assess psychopathology, quality of life, and level of physical activity.

As shown in Table 1, each consultation will have a central topic. The first session will cover the objectives of the intervention, emphasizing the achievement of greater well-being and the prevention of various cardiometabolic illnesses. The second session will explain the importance of food quality over calorie counting. In the third session, patients will be educated on identifying different macronutrients, their functions, and the relationship between insulin and weight regulation. The fourth session will provide various tips and types of diets to help patients incorporate this model into their own situations. The fifth session will focus on physical activity, highlighting the most efficient types for fat loss and the improvements that patients can implement. The sixth consultation will involve a follow-up to assess any difficulties in making changes and refine strategies to overcome them. After this consultation, the intervention will be concluded. The overall approach will focus on the progressive and flexible acquisition of habits, aiming to integrate changes into the patient’s daily life. This will occur within the therapeutic relationship established between the mental health nurse and the patient, utilizing a psychoeducational and non-blaming approach.

The consultations will use a previously developed guide, which will be provided to patients to allow them to review the information discussed during the sessions.

To improve adherence to the intervention protocol, participants will be called by phone two business days before their visits.

### 2.6. Control Group

Both the intervention group and the control group will continue their usual follow-ups within the EIP, attending consultations with their reference psychiatrist and receiving pharmacological or psychotherapeutic treatment as they did before the intervention. The control group will not receive any specific nursing consultations (beyond the administration of long-acting injectable antipsychotics where appropriate) or dietary or lifestyle advice during the follow-up. If patients in the control group require treatment or assistance for metabolic problems, they will be referred to primary care or endocrinology professionals, as was done previous to the intervention implementation.

### 2.7. Instruments and Variables

Sociobiographic data will be collected, including sex, age, marital status, living arrangement, educational level, medical diagnosis, time since the beginning of treatment, substance use, antipsychotic type and dose, mood stabilizer use, and whether patients are assisted by a primary caregiver (considered as such if they assist in 4 of the first 6 consultations).

The primary outcome will be weight loss, with a reduction of 5% considered clinically significant [38]. Secondary outcomes will include the establishment or non-establishment of metabolic syndrome according to the International Diabetes Federation (IDF) criteria [12], which consist of abdominal obesity (abdominal circumference ≥ 94 cm in men and ≥80 cm in women) plus two of the following four factors: (i) elevated blood triglycerides (≥150 mg/dL or treatment for it); (ii) decreased HDL-c (<40 mg/dL in men and <50 mg/dL in women); (iii) high blood pressure (systolic blood pressure ≥ 130 mmHg and diastolic blood pressure ≥ 85 mmHg or antihypertensive treatment); and (iv) elevated fasting glucose (≥100 mg/dL or previous diagnosis of type 2 diabetes).

Anthropometric variables (weight, height, BMI, waist circumference) and vital signs (resting blood pressure) will be measured using calibrated equipment provided by the hospital.

Laboratory values (fasting blood glucose, glycosylated hemoglobin, triglycerides, HDL, HDL/LDL ratio, C-reactive protein) will be collected in accordance with hospital policy.

To measure psychopathology, the Positive and Negative Syndrome Scale (PANSS) will be used. This scale consists of 30 items divided into three subscales: positive, negative, and general. The positive subscale measures symptoms such as hallucinations and delusions, the negative subscale measures symptoms such as flat affect and lack of motivation, and the general subscale measures symptoms such as agitation and hostility [37].

Depressive symptoms will be assessed using the Hamilton Depression Rating Scale (HAM-D), which consists of 17 items, with higher scores indicating greater severity of symptoms [39].

The EuroQol-5D (EQ-5D) scale will be used to evaluate a person’s subjective well-being in relation to their health. The scale consists of five dimensions: mobility, self-care, usual activities, pain/discomfort, and anxiety/depression [40].

Finally, the International Physical Activity Questionnaire (IPAQ) will be used to measure the level of reported physical activity. It consists of 8 questions that evaluate the amount and intensity of physical activity in different settings such as work, home, transportation, and leisure time. It also asks about vigorous and moderate physical activity, as well as sedentary activity [41].

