## 2. Methods

### 2.1. Design

This protocol is designed as an open-label, randomized clinical trial involving a group of patients in a first-episode psychosis (FEP) program, who will attend a series of nursing consultations focused on healthy habits aimed at addressing metabolic syndrome, in addition to their usual follow-up. The control group will consist of patients from the same program who will attend only routine nursing evaluation consultations.

The first author ([name]) will conduct the nursing consultations, based on a previously developed guide that structures and serves as a reference framework for the intervention.

This study was retrospectively registered on Clinical Trials—NCT06650943.

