### 2.8. Statistical Analysis

Categorical variables will be described as frequencies and percentages, while quantitative variables will be described as means and standard deviation (or medians and interquartile ranges where appropriate). Categorical variables will be compared using chi-square analysis or Fisher’s exact test, and quantitative variables will be compared using Student’s *t*-test, ANOVA, or the Mann–Whitney rank-sum test.

To compare changes in outcome variables between groups and over time, a multivariate mixed-effects model with repeated measures (linear or logit, depending on the characteristics of the variable) will be applied. Statistical significance will be assumed if the two-sided *p*-value is <0.05. The main analysis will assess the association between the study group and significant weight loss, defined as losing 5% of the original body weight.

To account for the potential effect of antipsychotics on weight and metabolic parameters, antipsychotics will be categorized as weight-increasing, weight-sparing, or as having non-conclusive effects. Sensitivity analyses will be conducted to examine the effect of each category on the outcomes. Categorization will be based on a review of previous evidence [42]. The use of weight-increasing antipsychotics in combination with weight-sparing antipsychotic use will be coded as weight-increasing antipsychotic use. The cumulative exposure of chlorpromazine-equivalent doses will then be calculated for each antipsychotic category in every patient [43].

Sensitivity analyses will also be conducted for each of the variables included in the previous section.

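### The caregiver variable is defined by attendance at post-allocation intervention sessions that controls do not have, so the sensitivity analysis planned on it cannot check the group effect

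*Protocol article*

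**What the plan says.** Section 2.7 (Instruments and Variables) includes, with sex, age, diagnosis and similar items, "whether patients are assisted by a primary caregiver (considered as such if they assist in 4 of the first 6 consultations".

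Section 2.8 (Statistical Analysis) states: "Sensitivity analyses will also be conducted for each of the variables included in the previous section". The section before it is 2.7, and no variable is excepted.

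Three places identify the six consultations and who has them:

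- Section 2.5 describes six themed sessions and says of the sixth: "After this consultation, the intervention will be concluded".
- Table 1 has a row "Mental health nurse consultation" under interventions, marked at weeks 1, 3, 5, 8, 12 and 16, all in post-allocation columns.
- Section 2.6 states: "The control group will not receive any specific nursing consultations", with an exception for giving long-acting injections. Section 2.1 describes controls as patients "who will attend only routine nursing evaluation consultations".

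**The concern.** A variable used to test the robustness of a randomised group effect should be fixed before randomisation, or at least be able to take the same values in both arms. This one is labelled as a background characteristic, but it is measured by what happens during the intervention. A control who lives with a highly involved caregiver has no route to being classed as accompanied.

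The risk is misreading. A caregiver-adjusted estimate that differs from the main estimate could be taken as evidence that the main result is fragile, or, if larger, as support for it. The difference could come entirely from how the variable is built.

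**Working it through.** **Step 1: can a control be coded 'yes'?** The definition needs attendance at 4 of 6 consultations. The numbered sessions of section 2.5 and Table 1 are exactly six and belong to the intervention. If the routine nursing evaluations of section 2.1 were counted instead, the full assessments take place "At the beginning of the study, and at 6 and 12 months from the start of the intervention". That is three time points, fewer than the four required. On the natural reading a control cannot qualify.

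**Step 2: the plan's own sample-size figure.** Section 2.9 gives a difference of 5, SD 7.5, 80% power and two-sided alpha of 5%. The normal approximation is 2 × (1.96 + 0.84)² × (7.5/5)² ≈ 35.3, so 36 per arm and 72 in total. The two-sample t-test version gives 36.3, so 37 per arm and 74 in total, which matches the stated 74. The illustration below uses 37 per arm and SD 7.5.

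**Step 3: what adjustment would estimate.** Assume controls are coded 'no', the variable enters the model beside group, and the outcome is percentage weight loss. Let p be the share of intervention participants coded 'yes', and g the mean extra weight loss of 'yes' over 'no' within that arm. Neither is in the document, so both are assumptions.

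Only three cells exist: controls, intervention 'no' and intervention 'yes'. The group coefficient is therefore the intervention 'no' mean minus the control mean. Call it e. The overall effect is (1 − p)·e + p·(e + g) = e + p·g. Setting this to 5 gives e = 5 − p·g.

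| p | g = −2 | g = 0 | g = 2 | g = 4 |
|---|---|---|---|---|
| 0.3 | 5.6 | 5.0 | 4.4 | 3.8 |
| 0.5 | 6.0 | 5.0 | 4.0 | 3.0 |
| 0.7 | 6.4 | 5.0 | 3.6 | 2.2 |

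A least-squares simulation with 4,000 trials per setting agreed with every cell to within 0.1.

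**Step 4: precision when there is no bias (g = 0).** The unadjusted standard error is 7.5 × √(1/37 + 1/37) = 1.74. With the caregiver term it is about 7.5 × √(1/37 + 1/(37(1 − p))), which gives 1.92, 2.14 and 2.57 for p = 0.3, 0.5 and 0.7. The simulation, which lets the number accompanied vary, gave 1.92, 2.15 and 2.62. Simulated power fell from about 0.81 to 0.72, 0.63 and 0.48.

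**Step 5: subgrouping instead.** The 'yes' stratum contains no controls, so it has no group effect to estimate. The 'no' stratum contrasts unaccompanied intervention participants with all controls, which is the comparison of Step 3 again.

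**The case against.** **The method is not stated.** Section 2.8 names no model for these analyses. Section 2.7 also contains the outcomes, so the sentence cannot literally be a covariate list. Controls might be coded as missing, or the comparison made only within the intervention arm. This stands: adjustment is an assumption, and those alternatives would avoid the bias in Step 3. They would still leave no between-group sensitivity analysis on caregiver support. The difficulty lies in the definition that the article fixes, and not in detail left to an analysis plan.

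**The word 'consultations' is used loosely.** The article also applies it to psychiatry visits and to the controls' routine evaluations. Table 1 marks weighing at every column without separating the arms. That controls cannot be 'yes' is therefore an inference, though a firm one. Both the drop-out rule in section 2.3 and section 2.5 use the term for the numbered nursing sessions. Even if other control visits were counted, attendance would still be recorded after allocation and at visits of a different kind.

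**The numbers are illustrative.** The main analysis is of a binary outcome, at least 5% loss, whereas the working uses a continuous one. A logit model would face the same empty cell, but the size of the shift on that scale was not calculated.

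**Antipsychotic exposure.** A reader might infer that the cumulative-dose variable has the same defect. Section 2.8 says: "The cumulative exposure of chlorpromazine-equivalent doses will then be calculated for each antipsychotic category in every patient". It gives no accrual window and does not say that the group effect is conditioned on this exposure. Participants may be up to five years past their first episode, so exposure before enrolment is an open reading. The text does not support calling this an error.

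**Conclusion.** The point holds for the caregiver variable. As defined, it cannot check the group effect, either by adjustment or by subgroup. Under the assumptions of Step 3 the adjusted coefficient runs from 2.2 to 6.4 against a true 5. The direction depends on the sign of g, and at g = 0 only precision is lost.

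A reader might go further and conclude that the randomised comparison itself is compromised. It is not: the main unadjusted comparison, the primary outcome and the sample size do not involve this variable. Nor is it an error to leave antipsychotic category to sensitivity analyses, because randomisation makes the main comparison valid without it, and section 2.8 does not list the mixed model's covariates. Severity is minor to moderate.

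**What to change.** 1. Record at enrolment, in both arms, whether a caregiver supports the participant, and use that in the sensitivity analysis.
2. Report caregiver attendance at sessions descriptively, within the intervention arm only.
3. State that any variable used to adjust the group effect takes its pre-randomisation value.
4. State the accrual window for cumulative antipsychotic exposure. If it includes follow-up, label that analysis exploratory.

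The cost is one enrolment question and a few sentences of wording. For anyone already enrolled, the answer would have to come from clinical records.

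Optionally, baseline antipsychotic category and baseline weight could be prespecified as covariates in the main model. Three categories cost two degrees of freedom and baseline weight one. This may gain precision and corrects no error.

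### The metabolic syndrome rule keeps treated triglycerides and treated blood pressure positive but scores low HDL on the measured value alone, so treatment during follow-up can change a participant's status

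*Protocol article*

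**What the plan says.** Section 2.7 of the protocol article names the outcome: "Secondary outcomes will include the establishment or non-establishment of metabolic syndrome". It cites the International Diabetes Federation criteria (reference 12) and then writes the rule out as abdominal obesity "plus two of the following four factors". The four factors read:

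- Triglycerides: "i) elevated blood triglycerides (≥150 mg/dL or treatment for it".
- HDL: "ii) decreased HDL-c (<40 mg/dL in men and <50 mg/dL in women".
- Blood pressure, after a systolic threshold: "diastolic blood pressure ≥ 85 mmHg or antihypertensive treatment".
- Glucose: "iv) elevated fasting glucose (≥100 mg/dL or previous diagnosis of type 2 diabetes".

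Three other places bear on whether treatment can start between assessments. Section 2.3 excludes people prescribed a hypoglycemic drug before or during the study and names no lipid-modifying drug. Section 2.6 says of controls with metabolic problems that "they will be referred to primary care or endocrinology professionals". Section 2.5 puts the laboratory assessments at baseline, 6 months and 12 months.

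**The concern.** Three of the four factors have a clause that keeps them positive once the measured value is back to normal: treatment for triglycerides and blood pressure, an earlier diagnosis for glucose. HDL has none. Two participants with equally well-treated abnormalities can therefore be scored differently, depending on which abnormality was treated. Since the outcome is a yes/no status that turns on a count of two, losing one factor can reverse it. A change produced by a drug would then appear in the results as absence of metabolic syndrome.

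**Working it through.** The plan states no figure on this point, so there is none to reproduce. The check applies the written rule to every possible case.

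**Inputs (section 2.7).** Abdominal obesity is present. Status is positive if at least 2 of 4 factors are positive. The participant has low HDL at baseline, and HDL is at or above the cut-off later, under treatment. Let k be the number of other positive factors among triglycerides, blood pressure and glucose. Each is yes or no, so there are 2 × 2 × 2 = 8 profiles.

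**Formulas.**
- Baseline count = k + 1.
- Later count, rule as written = k, because HDL is no longer below the cut-off.
- Later count, with a treatment clause on HDL = k + 1.

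| k | Profiles | Baseline | Later, as written | Later, with HDL clause |
|---|---|---|---|---|
| 0 | 1 | 1, no | 0, no | 1, no |
| 1 | 3 | 2, yes | 1, **no** | 2, yes |
| 2 | 3 | 3, yes | 2, yes | 3, yes |
| 3 | 1 | 4, yes | 3, yes | 4, yes |

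Status changes in 3 of 8 profiles as written (all of k = 1) and in 0 of 8 with the clause.

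**Comparison within the rule.** Take a participant with high triglycerides and high blood pressure as the two factors, and let treatment normalise either one. The count stays at 2 and the status stays positive. Replace one of these with low HDL, normalise that by treatment, and the count falls to 1.

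**Offset through triglycerides.** Suppose the drug that raised HDL is also counted as triglyceride treatment. For the three k = 1 profiles under the written rule:
- Other factor blood pressure: HDL is lost and triglycerides are gained, 2 − 1 + 1 = 2, status kept.
- Other factor glucose: the same, 2 − 1 + 1 = 2, status kept.
- Other factor triglycerides: that factor is already positive and nothing is gained, 2 − 1 = 1, status lost.

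The offset therefore covers two of the three profiles, and only if the drug is coded that way.

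**Can it occur in this trial?** Lipid-modifying drugs are not among the exclusions in section 2.3. Section 2.6 provides a referral route for metabolic problems. Treatment can therefore begin between the baseline, 6-month and 12-month assessments.

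**The case against.** The strongest reply is that section 2.7 paraphrases a cited standard in a condensed article. If the cited criteria have a treatment clause for HDL, the omission is only an abbreviation. If they do not, adding one departs from the named standard. The documents cannot settle which. This stands as a reason to check the source before editing. It does not remove the point, because the article writes the rule out in full and no other section supplies the clause.

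The rule is also not uniform apart from HDL: the glucose factor has a diagnosis clause, not a treatment clause. That is true but matters little. A diagnosis persists, and hypoglycemic drugs are excluded, so the gap is specific to HDL.

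A reader might go further and infer that controls, who receive no lifestyle advice, will be treated more often, so that their rate of metabolic syndrome is understated and the comparison is pulled toward no difference. A reader might also attach a size: if 2 to 4 of 44 controls were affected, 2/44 = 4.5% and 4/44 = 9.1%. The documents support neither step. Section 2.6 mentions neither HDL nor lipid drugs, says that both groups continue usual care, and does not say that intervention patients are denied referral. There is no HDL distribution and no rate of lipid treatment. The 2 to 4 would have to be participants with exactly two factors including low HDL who all start treatment, all reach the cut-off and all miss the triglyceride offset. The 44 is the recruitment target per arm, before dropout.

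Finally, HDL and triglycerides are collected as laboratory values in their own right, so the yes/no status is not the only view of a lipid change.

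**Conclusion.** The inconsistency is in the text of section 2.7, and its consequence follows from the rule. A participant with abdominal obesity, low HDL and exactly one other factor is scored free of metabolic syndrome once treatment brings HDL to the cut-off, unless the same drug is counted under triglycerides and so makes good the lost factor. That is 3 of 8 logical profiles as written, 1 of 8 if the triglyceride offset always applies, and 0 of 8 with a treatment clause. These counts say nothing about how many participants would be affected. Size and direction between arms cannot be determined from the documents.

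This is a minor point. It concerns one secondary outcome and leaves the primary weight outcome and the sample size as they are. It rests on the wording of section 2.7 and on lipid-modifying treatment being possible during follow-up. It does not rest on what the cited criteria say.

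**What to change.** Check the HDL factor in section 2.7 against the cited criteria, then put it on the same footing as triglycerides and blood pressure by adding *or treatment for it* after the HDL cut-offs. If the cited criteria differ, say that the rule departs from them. Apply the same rule at baseline, 6 and 12 months, and settle it before metabolic syndrome status is derived.

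Record lipid-modifying treatment at each assessment, with the abnormality it was given for. The triglyceride factor already needs this, while the drugs named among the variables in section 2.7 are antipsychotics and mood stabilizers. State which factor a lipid drug counts toward. If one drug counted under both, a participant with low HDL alone would go from 1 factor to 2 simply by starting treatment.

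The cost is a few words and one recorded item. The small downside is that a treated participant whose HDL has normalised stays positive, as already happens for triglycerides and blood pressure. The measured HDL values, which are collected anyway, will still show the change.
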